# Protocol for a matched-pair cluster control trial of ARCHES (Addressing Reproductive Coercion in Health Settings) among women and girls seeking contraceptive services from community-based clinics in Nairobi, Kenya

**DOI:** 10.1186/s12978-020-00916-9

**Published:** 2020-05-27

**Keywords:** Global health, Contraception, Gender-based violence, Reproductive coercion, Intimate partner violence, Sexual gender-based violence, Sub-Saharan Africa, Adaptation, Kenya, Protocol

## Abstract

**Background:**

Reproductive coercion (RC) and intimate partner violence (IPV) are prevalent forms of gender-based violence (GBV) associated with reduced female control over contraceptive use and subsequent unintended pregnancy. Although the World Health Organization has recommended the identification and support of GBV survivors within health services, few clinic-based models have been shown to reduce IPV or RC, particularly in low or middle-income countries (LMICs). To date, clinic-based GBV interventions have not been shown to reduce RC or unintended pregnancy in LMIC settings.

**Intervention:**

ARCHES (Addressing Reproductive Coercion in Health Settings) is a single-session, clinic-based model delivered within routine contraceptive counseling that has been demonstrated to reduce RC in the United States. ARCHES was adapted to the Kenyan context via a participatory process to reduce GBV and unintended pregnancy among women and girls seeking contraceptive services in this setting. Core elements of ARCHES include enhanced contraceptive counseling that addresses RC, opportunity for patient disclosure of RC and IPV (and subsequent warm referral to local services), and provision of a palm-sized educational booklet.

**Methods:**

A matched-pair cluster control trial is being conducted to assess whether the ARCHES intervention (treatment condition), as compared to standard-of-care contraceptive counseling (control condition), reduces RC and IPV, and improves contraceptive outcomes for woman and girls of reproductive age (15 to 49 years) seeking contraceptive services from community-based clinics in Nairobi, Kenya. All six clinics were assigned to intervention-control pairs based on similarities in patient volume and demographics, physical structure and neighborhood context. Survey data will be collected from patients immediately prior to their clinic visit (baseline, T1), immediately after their clinic visit (exit), and at 3- and 6-months post-visit (T2 and T3, respectively).

**Discussion:**

This study is the first to assess the efficacy of an adaptation of the ARCHES model to reduce GBV and improve reproductive health outside of the U.S., and one of only a small number of controlled trials to assess reductions in GBV associated with a clinic-based program in an LMIC context. Evidence from this trial will inform health system efforts to reduce GBV, and to enhance female contraceptive control and reproductive health in Kenya and globally.

**Trial registration:**

Registered May 23, 2018 - ClinicalTrials.gov, NCT03534401. Unique Protocol ID: 170084.

## Plain English summary

Gender-based violence, including reproductive coercion (RC; behaviors by male partners or others to interfere with women’s and girls’ contraceptive use and pregnancy decisions) and intimate partner violence (IPV; violence perpetrated by a current or former romantic partner), contribute to unintended pregnancy among women and girls globally. Few clinic-based model have been shown to reduce experiences of GBV, particularly in low or middle-income countries (LMICs). ARCHES (Addressing Reproductive Coercion in Health Settings) is a single-session intervention delivered within clinic-based contraceptive counseling session designed to address RC and IPV and has been demonstrated to reduce RC in the United States. ARCHES was adapted to the Kenyan context to reduce GBV and unintended pregnancy among women and girls seeking contraceptive services in this setting. This protocol describes the adaptation and evaluation of ARCHES underway in six community-based clinics (3 intervention, 3 control) in Nairobi, Kenya. This evaluation trial will assess whether ARCHES, as compared to routine contraceptive counseling, reduces RC and IPV, and improves contraceptive use and control among woman and girls of reproductive age (15 to 49 years). This study is the first to assess the efficacy of an adaptation of the ARCHES model outside of the U.S. Results from this study will be used to inform health system efforts to reduce GBV and improve the reproductive health and empowerment of women and girls in Kenya and globally.

## Background

Approximately 1 in 3 women worldwide will experience physical or sexual intimate partner violence (IPV) in their lifetime [1], an epidemic which contributes to female morbidity and mortality globally. Women and girls of reproductive age who seek contraceptives in health settings report higher rates of IPV than their same age peers [2–4], and those experiencing this form of gender-based violence (GBV) are significantly more likely to report unintended pregnancies and other poor sexual and reproductive health (SRH) outcomes [5–8]. Women and girls experiencing such abuse also report higher incidence of male partner opposition to their use of contraceptives [2, 9–11]. In 2018, the *Lancet Commission on Sexual and Reproductive Health and Rights* found that GBV was a significant contributor to global unmet need for contraception and unintended pregnancy, with the greatest proportion and relative impacts of GBV experienced by women and girls in low and middle-income countries (LMICs) [12].

Reproductive coercion (RC) is defined as controlling behaviors by male partners or family members to reduce women’s and girls’ reproductive autonomy [13] in the forms of limiting her access to or use of contraceptive methods, coercion to become pregnant against her will, and control of decisions to maintain or terminate a pregnancy [14]. A growing body of evidence demonstrates that RC is independently associated with unintended pregnancy, beyond the effects seen for IPV alone [2, 11, 15, 16], lending support to the hypothesis that this understudied form of GBV is a mechanistic link explaining, at least in part, the consistently-demonstrated associations between IPV and poor SRH outcomes [11]. While research describing the burden of RC in LMIC contexts is still at its inception, initial studies confirm the high prevalence of RC (as perpetrated by both male partners and in-laws) and its connection to experiences of unintended pregnancy [17] – an association which has been previously demonstrated in the United States [2, 8, 11].

In 2013, based on the growing understanding of the negative effects of GBV on the health of women and girls, and the need to address GBV as a human rights abuse, the World Health Organization (WHO) issued global guidelines recommending the identification and support of IPV survivors within health services [18]. This guidance was updated in 2019 to include the identification of RC [19]. Despite this global call-to-action, to date, only one clinic-based GBV prevention intervention has been shown via experimental or quasi-experimental design to reduce women’s experience of IPV in an LMIC context [20–22] and none have addressed RC or increased female contraceptive control. Although an important advance, this model was limited to women in the third trimester of pregnancy, and required [4] two-hour sessions with a counselor not providing routine care [22], making it challenging to integrate this intervention into existing routine health services.

ARCHES (Addressing Reproductive Coercion in Health Settings) is a brief, clinic-based intervention integrated within routine contraceptive counseling to address RC and IPV. It was developed and evaluated in the United States by a consortium of researchers from the University of Pittsburgh and the University of California San Diego, and practitioners from the U.S.-based NGO Futures without Violence. In two U.S.-based cluster randomized control trials (cRCTs) with over 4000 women and girls seeking care from reproductive health clinics, ARCHES was shown to reduce women’s and girls’ experiences of RC compared to standard-of-care contraceptive counseling [23, 24]. Importantly, women and girls receiving ARCHES also were more likely to report leaving a relationship that they considered unsafe or unhealthy, likely reducing their exposure to IPV, and to report increased knowledge and sharing of referral information for local IPV services [23, 24]. Based on this promising evidence, a consortium of researchers and practitioners led by the University of California San Diego (UCSD) and including the International Planned Parenthood Federation (IPPF), IPPF Africa Regional Office (ARO), Family Health Options Kenya (FHOK; NGO operating community-based health services), and Population Council in Kenya, set out to adapt and evaluate the ARCHES model in Nairobi, Kenya.

### Hypotheses

We hypothesize that women and girls age 15–49 years seeking contraceptives services from NGO-operated, community-based clinics in Nairobi, Kenya who receive the ARCHES intervention (treatment condition) will experience greater reductions in RC and IPV, and increases in uptake of modern contraceptive methods (primary outcomes), as compared to same age women and girls seeking these same services and receiving standard-of-care contraceptive services (control condition) at 3 and 6 months post-visit. We further hypothesize that the same women and girls receiving ARCHES will report decreased incident pregnancy (both overall and unintended) and attitudes accepting of RC and IPV and increased self-efficacy to use contraceptives (including in the face of RC), covert use of contraceptives (among those reporting RC), awareness and utilization of IPV services, and leaving a relationship because it felt unsafe or unhealthy as compared to those women and girls receiving standard-of-care services.

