**Fig. 1 Fig1:**
[figure not shown]
Study design

**Table 1 Tab1:** Outcome measures

Outcomes	Participant Survey measurement points				Analysis metric		Measures
	T1		T2	T3			
	*Baseline*	*Exit*	*3 month follow-up*	*6 month follow-up*	*Change from baseline to follow-up*	*Follow-up value only*	
*Primary outcomes for all participants*							
Reproductive Coercion in past 3 months	X		X	X	X		RC Scale (RCS; 9 items) [25] (binary)
Physical IPV and Sexual IPV in past 3 months	X		X	X	X		Conflict Tactics Scale-2 (CTS2; 7 items) [26] (binary) Sexual Experiences Survey (1 item) [27] (binary)
Uptake of female controlled contraceptive method		X				X	Self-report (1 item)
*Secondary outcomes for all participants*							
Incident and unintended pregnancy past 6 months			X	X		X	National Survey of Family Growth (NSFG; 1 item) [28, 29] (binary)
Self-efficacy to utilize contraceptives in the face of RC	X		X	X	X		Investigator-developed (4 items) [23, 24] (summary score)
Knowledge of IPV services					X		Investigator-developed (4 items) [23, 24] (summary score)
Reduced acceptability of RC and IPV	X		X	X	X		Investigator-developed (8 items) [23, 24] (summary score) Kenya Demographic and Health Survey (DHS) (7 items) [30] (summary score)
*Secondary outcomes for those reporting RC and/or IPV at baseline*							
Covert use of contraceptives in the face of RC in the past 3 months	X		X	X	X		WHO Multi-country Study on Women’s Health and Domestic Violence against Women (1 item) [10] (binary)
Utilization of IPV services among those reporting IPV in the past 3 months			X	X		X	Investigator-developed (8 items) [23, 24] (binary)
Leaving a relationship because it felt unsafe or unhealthy among those reporting RC or IPV in the past 3 months			X	X		X	Investigator-developed (1 item) [23, 24] (binary)

All measures were adapted for use in the current study via cognitive interviews with Kenyan contraceptive care patients and providers

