#### Uptake of a modern contraceptive method

Report of receiving a modern contraceptive method during the clinic visit (binary, yes/no) will be assessed using a single item, “Did you receive a family planning method today from your provider?” with confirmation provided via a follow-up question regarding which method they received from a list of all available methods (i.e. IUD, implants, injection, contraceptive pills). The patch, vaginal ring and female condom are not included as they are not commonly utilized or available methods in this setting. Additionally, because the ARCHES intervention focuses on increasing uptake and understanding of female controlled contraceptive methods that are easy to use discretely to reduce RC, the male condom will be excluded from this measure.

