### Data analysis

We will adopt a difference-in-differences approach utilizing a multilevel, mixed-effects generalized linear regression, with logistic specifications for binary outcomes and linear specifications for continuous or scale outcomes, to evaluate associations between ARCHES intervention exposure and primary and secondary outcomes overtime. Longitudinal models will have fixed effects including time (baseline or follow-up), treatment arm, clinic, selected covariates, and a time and treatment interaction to indicate the treatment effect. These models will also take into account clusters (i.e. clinics) and clustering within clinics using nested random effects specifications to account for repeated measurements over time of individuals nested within clusters. The comparisons of outcomes at a single time point (e.g. immediately post-intervention) will use a similar multilevel mixed-effects regression approach, with single-level random effect specifications only for clinic, and only a fixed treatment effect (rather than time by treatment comparison). Final analyses will adjust for potentially relevant covariates (age, parity, food insecurity within the past 30 days, marital status, highest level of education attended, language of survey administration), in addition to time and treatment condition. Descriptive and bivariate analyses will be used to assess frequencies of and differences in demographics by treatment and loss to follow-up. Any characteristics identified as significantly associated with treatment or loss to follow-up at the *p* < 0.20 threshold will be considered as potential covariates (fixed effects) in adjusted models assessing effects of the intervention. Backwards selection at *p* < 0.20 will be used to finalize inclusion of potential covariates in regression models. Collinearity of covariates will be assessed, and highly collinear covariates may be removed from final models.

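### Uptake, a primary outcome, is hypothesised at 3 and 6 months but measured only at exit, and the exit contrast is open to confounding by client mix

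*Protocol article*

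**What the plan says.** **Hypothesis.** The Hypotheses section lists "increases in uptake of modern contraceptive methods (primary outcomes") in one sentence with reproductive coercion (RC) and intimate partner violence (IPV). The comparator and timing close that sentence: "receiving standard-of-care contraceptive services (control condition) at 3 and 6 months post-visit".

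**Measurement.** In Table 1 the row "Uptake of female controlled contraceptive method" is marked at exit only, with the follow-up value as its metric. Its baseline, 3-month and 6-month cells are blank. The outcome section says: "Report of receiving a modern contraceptive method during the clinic visit (binary, yes/no) will be assessed using a single item". The item is "Did you receive a family planning method today from your provider", followed by a question on which method. The male condom is excluded.

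**Analysis.** For outcomes followed over time, the Data analysis section states: "We will adopt a difference-in-differences approach utilizing a multilevel, mixed-effects generalized linear regression". Outcomes at a single time point get "only a fixed treatment effect (rather than time by treatment comparison"). The named covariates are age, parity, food insecurity, marital status, education and survey language.

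**Allocation.** Clinics were paired on patient volume, patient characteristics (wealth, age, services sought) and community type. They were not randomised within pairs: those nearer the implementing organisation's headquarters were more likely to receive ARCHES. Women fall into an arm according to the clinic they attend.

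**The concern.** Two things are at stake. First, a primary hypothesis is tied to time points at which its outcome is not collected. A reader of the eventual report could not tell whether an exit result confirms the stated hypothesis or replaces it.

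Second, RC and IPV are compared as changes from baseline, which removes stable differences between the arms on the model's scale. Uptake has no such protection, in a design where neither clinics nor women were randomised. Eligibility admits women who come for family planning and women who are only interested in it, and on reproductive status excludes only those pregnant or sterilised. A woman already using a method who leaves with nothing new is scored no. The proportion scored yes therefore depends partly on who walks in, which ARCHES does not cause.

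**Working it through.** **1. Timing, side by side.**

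| Source | Time of uptake |
|---|---|
| Hypotheses | 3 and 6 months post-visit |
| Table 1 | Exit only |
| Outcome definition | The clinic visit, that day |
| Data analysis | Single-time-point model |

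Neither of the two hypothesised time points is measured. The item's own wording shows that the blank cells in Table 1 are not an extraction fault.

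**2. The plan's own sample-size figure.** It concerns RC only. An odds ratio of 0.4 applied to 17.1% gives 7.62%. Two-sided 5% significance and 80% power then need 189 per arm. The design effect is 1 + ((1 + 0.5²) × 68 − 1) × 0.001 = 1.084, and 189 × 1.084 = 204.9, against 204 stated. For retention, 408 / 0.75 = 544, as stated. The figure reproduces, but no rate or effect is given for uptake, so it neither supports nor refutes this point.

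**3. Size of possible bias, on assumed rates.** From the protocol: 600 women (taken as 300 per arm), mean cluster size 100, coefficient of variation 0.5 and ICC 0.001, so the design effect is 1 + (1.25 × 100 − 1) × 0.001 = 1.124. The ICC was set for RC and is borrowed here.

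Assumed: a share s of women come for a method and receive one with probability a; the others receive one with probability b. These probabilities are the same in both arms, so there is no true effect. Then:

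- uptake = s·a + (1 − s)·b in each arm;
- SE = √[1.124 × (p₁(1 − p₁) + p₀(1 − p₀)) / 300];
- false-positive rate = two-sided rejection at 1.96, normal approximation.

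Example: a = 0.9, b = 0.5, s = 70% vs 50%. Uptake is 0.63 + 0.15 = 0.78 vs 0.45 + 0.25 = 0.70. The odds ratio is (0.78/0.22) / (0.70/0.30) = 1.52. SE = √[1.124 × (0.1716 + 0.2100) / 300] = 0.0378, z = 0.08 / 0.0378 = 2.12, and the false-positive rate is 56%.

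| Share coming for a method | a = 0.9, b = 0.5 | a = 0.9, b = 0.7 | a = 0.8, b = 0.6 |
|---|---|---|---|
| 55% vs 50% | OR 1.10; 8% | OR 1.07; 6% | OR 1.05; 6% |
| 60% vs 50% | OR 1.22; 18% | OR 1.14; 9% | OR 1.10; 8% |
| 70% vs 50% | OR 1.52; 56% | OR 1.31; 23% | OR 1.22; 18% |

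The second entry in each cell is the false-positive rate, nominally 5%. If the imbalance ran the other way, the odds ratios would be the reciprocals (0.66 to 0.95) and a real benefit could be masked.

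**4. What the plan does against this.** Matching on services sought addresses the right variable, but at clinic level, in three pairs, with no achieved balance reported. The named covariates include neither method in use on arrival nor reason for visit.

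**The case against.** The best defence is that the timing conflict is a drafting slip. Table 1, the outcome definition and the analysis section agree on an exit outcome with a single-time-point model; one long sentence attaches one time phrase to three outcomes. That is probably how it arose, but the sentence is the statement of the primary hypotheses and has to be right.

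Several stronger readings are tempting, and the document does not support them:

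- **That uptake cannot be tested at all.** An exit contrast is defined, measured and modelled. Only the 3- and 6-month claim is untestable.
- **That the exit contrast is confounded.** No imbalance is shown. Pairs were matched on services sought, and a continuing pill or injection user who is resupplied answers yes. Only women with a method in place who receive nothing are misread, and their share is not given.
- **That the outcome has two competing definitions.** The outcome section gives one operational list and explains the condom exclusion. The labels differ; the measure does not.
- **That a large bias is likely.** If 90% of women needing a method get one, and 20% vs 30% are already protected and receive nothing, uptake is 72% vs 63% (odds ratio 1.51). That is one assumed scenario near the top of the range. At a 5-point imbalance the false-positive rate is close to nominal.

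It is also fair that receipt at a visit has no pre-visit value, so the missing baseline follows from the choice of outcome, which is legitimate for a single-session intervention. The questionnaire is not shown and may already record the current method. The p < 0.20 screen refers broadly to characteristics, but it follows a sentence about demographics and commits to nothing on this variable.

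**Conclusion.** The point holds in two parts. The contradiction is certain: the primary uptake hypothesis is set at 3 and 6 months, and the outcome is measured at neither. The exit comparison that can be made is open to confounding by client mix, because it alone among the primary outcomes lacks baseline differencing under non-random allocation, and the most relevant covariate is not named. The size of any bias cannot be computed from the document. The spurious odds ratio of about 1.05 to 1.52, with false-positive rates of 6% to 56%, rests on assumed receipt rates and imbalances of 5 to 20 points, and on the protocol's RC-based ICC. It shows what is possible, not what is expected.

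**What to change.** 1. Restate the uptake hypothesis as receipt of a female-controlled modern method (male condom excluded) at the exit survey. Keep the 3- and 6-month timing for RC and IPV. Use that one label in the Hypotheses, Table 1 and the outcome section.
2. Name method in use on arrival and reason for visit, taken from the baseline survey, as prespecified covariates in the exit uptake model, kept regardless of the p < 0.20 selection. Add a baseline item if either is not already collected.
3. Report the uptake result as a non-randomised comparison.

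The cost is wording and at most a short addition to the baseline survey. The downside is that women already enrolled may lack the information if the survey does not already record it; the adjusted analysis would then cover only part of the sample, since the plan imputes nothing.

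A current-method item at 3 and 6 months is optional. It measures a different quantity, and is needed only if the sponsor wants to keep an uptake hypothesis at those times. Redefining uptake as leaving the visit covered by a method would also change what is estimated and is not required.

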### Study overview and design

We will test our hypotheses using a matched-pair, cluster-controlled design with the two parallel treatment groups assigned in a 1:1 allocation ratio (ClinicalTrials.gov ID: NCT03534401). Eligible female patients seeking contraceptive care services from clinics allocated to the intervention or control condition will complete surveys at baseline prior to their clinical visit (T1), immediately after their visit before leaving the clinic (T2; i.e. exit survey), 12–16 weeks post-visit (T3; i.e. 3-month follow-up survey), and 23–26 weeks post-visit (T4; i.e. 6-month follow-up survey). We designed this superiority trial with sufficient power (*N* = 600) to assess our hypothesized short (3-month) and longer-term (6-month) outcomes. See Fig. 1. Study design and Table 1. Outcome measures.

